## **. Sample size**

Since, there was no similar research carried out in Nepal thus the sample size has been calculated based on the similar study conducted by JW Muchiri et al., (2010) in South Africa where, mean+ SE of HbA1c percentage in both intervention and control group was 9.67±0.29 Vs 10.30±0.29 respectively ^20^. Based on this consideration, JW Muchiri et al., (2010) data will be used to calculate the sample size taking α level of significance at 5% and power of 90%. The sample size will be calculated using test comparing independent two means in STATA/MP version 14.1 (StataCorp LP, College Station, Texas). The following formula with 5% significance level (Zα/2 = 1.96) and 90% power (Zβ) will be used.

Where

Z_α_ = Z value for α error

Z_β_ = Z value for β error

S = Common standard deviation between two groups

d = clinically meaningful difference

Z_α_=1.96, Z_β_= 1.282, S= 0.1, d= -0.64

The sample size will be calculated 108 (54 participants in each arm). Thus, the sample size will be adjusted with 20% non-response rate and 25% loss through follow-up and drop out the total sample size will be 156 (78 participants in Intervention and 78 participants in usual care arm respectively.)

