**Exclusion Criteria:**

- Those who are pregnant women, lactating women or planning to become pregnant during

the course of study.

- Those who are severely ill or more than two comorbidities
- Those who have any plan to migrate from the study area for at least 1 year
- HbA1c ≥93mmol/mol (10.5%)
- Those who are on insulin therapy

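### The printed sample-size inputs (S = 0.1, d = -0.64) give about 1 patient per arm, not 54; the SD of about 1.0 that yields 54 is neither stated nor derived, so the 90% power is unsupported

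*Protocol*

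**What the plan says.** The Sample size section of the protocol bases the calculation on one earlier trial in South Africa, from which it quotes "mean+ SE of HbA1c percentage in both intervention and control group was 9.67±0.29 Vs 10.30±0.29 respectively". The design targets are set by "taking α level of significance at 5% and power of 90" percent, and the test is two-sided: "The following formula with 5% significance level (Zα/2 = 1.96) and 90% power (Zβ) will be used". The software and method are also named: "The sample size will be calculated using test comparing independent two means in STATA/MP version 14.1".

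The spread is defined as "S = Common standard deviation between two groups", and d as the clinically meaningful difference. The values entered are "Z_α_=1.96, Z_β_= 1.282, S= 0.1, d= -0.64". The result is "The sample size will be calculated 108 (54 participants in each arm"), which is then raised for non-response and loss to follow-up to 156 in total, 78 per arm.

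The section gives no arm sizes for the source trial, no conversion from standard error to SD, and no other basis for S.

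**The concern.** The protocol's sample size and its 90% power for HbA1c rest on this single calculation. Three of its printed figures do not fit together:

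- S = 0.1 is far too small to lead to 54 per arm when the difference is 0.64.
- S = 0.1 is smaller than the standard error of 0.29 quoted a few lines above it. A standard deviation cannot be smaller than the standard error of a mean from the same data.
- d = -0.64 does not match the quoted means, 9.67 and 10.30.

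A reader cannot get from the inputs to the result, and cannot tell which SD was used or where it came from. At stake is how the trial will be read. If it finds no difference in HbA1c, that result will be taken as coming from a trial with 90% power, and the protocol does not give the figures needed to support that.

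**Working it through.** **Inputs, all from the Sample size section.** Zα/2 = 1.96 (two-sided 5%), Zβ = 1.282 (90% power), S = 0.1, d = -0.64; source means 9.67 and 10.30, each with SE 0.29; stated result 54 per arm. Allocation is equal (section 7.2). The formula itself is not legible in the text at hand. I assume the standard one for two independent means, which uses exactly the symbols listed:

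n per arm = 2 (Zα/2 + Zβ)² S² / d², with (1.96 + 1.282)² = 3.242² = 10.51.

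**Step 1: the printed inputs.** n = 2 × 10.51 × 0.1² / 0.64² = 0.2102 / 0.4096 = 0.51, rounded up to 1 per arm. An exact t-based calculation gives 3 per arm. The stated 54 is not reproduced.

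**Step 2: the other printed measure of spread.** With the SE of 0.29 used as if it were the SD, n = 2 × 10.51 × 0.29² / 0.64² = 4.3, that is 5 per arm (t-based: 6). Taking d = 0.63, or a one-sided test, does not bring either value of S near 54.

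**Step 3: which inputs give 54.** The quoted means differ by 10.30 − 9.67 = 0.63.

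| S | d | n per arm, normal formula | n per arm, t-based |
|---|---|---|---|
| 1.0 | 0.63 | 53 | 54 |
| 1.0 | 0.64 | 52 | 53 |

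Solving the normal formula backwards, S = d √(54/2) / 3.242, which is 1.01 for d = 0.63 and 1.03 for d = 0.64. The result of 54 therefore needs an SD of about 1.0. The match is exact for S = 1.0 and d = 0.63 with the t-based two-means calculation, the kind of test that the section names.

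**Step 4: does an SD of 1.0 follow from the quoted SE?** For a simple mean, SD = SE × √n, so n = (1.0 / 0.29)² = 11.9. The SE and the SD agree only if the source arms held about 12 patients each. The protocol does not say how many they held.

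**Step 5: how far power depends on this number.** Illustration only, because the SD is not given. Two-sided 5%, d = 0.63, 54 completers per arm, noncentral t:

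| SD (assumed) | Power |
|---|---|
| 1.0 | 90.0% |
| 1.15 | 80.5% |
| 1.3 | 70.4% |
| 1.5 | 58.0% |

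At S = 0.1, as printed, 54 per arm would have essentially 100% power.

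**The case against.** The best answer is that this is a slipped decimal. S = 1.0 with the quoted means gives exactly 54 in the type of calculation that the section says was run, and the step from 0.63 to 0.64 may be rounding, worth one or two patients per arm. I think this is probably what happened, and it disposes of any suggestion that 54 was invented. It does not supply a reason for the SD of 1.0, which the section neither states nor derives.

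A second answer is that an SD near 1.0 is plausible here. The Exclusion Criteria remove patients at "HbA1c ≥93mmol/mol (10.5"%) and the Project summary enrols above 6.5%. If both limits apply at entry, baseline values span at most 4 points: an even spread over that range has SD 4/√12 = 1.15, and no distribution within it can exceed 2.0. This is indicative only, because the Inclusion Criteria tie the lower limit to the time of diagnosis and follow-up values are not bounded. The primary outcome in the Project summary is also a difference in mean change, whose SD can be smaller or larger than that of a single HbA1c value. So the argument is available, but the protocol does not make it.

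A reader might go further and infer that the trial is underpowered, by scaling the SE of 0.29 up to source arms of, say, 30 or 50. The documents do not support that. They give no source arm sizes, and they do not say whether the SEs are raw or model-adjusted, or at which visit they were taken. Nor does the closeness of the source control mean (10.30) to the 10.5% limit show that the calculation is wrong. It is only a reason to say why the source's spread should carry over.

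**Conclusion.** The sample-size calculation is wrong as written. The printed inputs give 0.51, about 1 per arm, against a stated 54; S = 0.1 cannot be the SD of data with an SE of 0.29; and d disagrees with the quoted means by 0.01. The first two are certain, given the standard formula and SEs in the ordinary sense. That S = 0.1 stands for 1.0 is a strong inference from the exact match at 54, not something the protocol says.

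Once the decimal is corrected, the sum works and the justification is still missing: an SD of 1.0 agrees with the only quoted measure of spread just when the source arms held about 12 patients. The 90% power is thus unsupported. It would be too strong to say that the protocol's figures fail to deliver it, since 54 per arm has 90% power at S = 1.0 and nearly 100% at S = 0.1. The fall from 90% to 58% between SD 1.0 and SD 1.5 shows why the SD needs a source; it is not an estimate of this trial's power. Nothing here invalidates the randomised comparison or shows that 156 is too few.

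**What to change.** In the Sample size section:

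1. Replace S = 0.1 by the SD actually used, and give its source: either SE × √n with the arm size of the source trial, or an SD for change in HbA1c, the stated primary outcome, suited to the eligible HbA1c range.
2. Make d agree with the quoted means (0.63), or keep another value and justify it as a clinically meaningful difference.
3. Restate the power that the planned 156 gives at that SD, naming the number of completers per arm assumed, with a short table of power by SD.

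The cost is protocol wording only. No patients are added and no procedure changes. The downside is that the stated power may become less favourable than 90%.

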# **Project summary (~250 words)**

Diabetes mellitus is one of the major intractable public health problems in developing countries including Nepal. The dietary approach is of paramount significance in the management of type 2 diabetes. There is still a lack of evidence on a dietitian-led dietary approach to the management of T2DM patients in the Nepalese context. The aims of this study is to examine the effectiveness of dietitian-led dietary approach to management of diabetes on reduction of HbA1c level, nutrition education score and macronutrient intake among T2DM patients in a tertiary care hospital in Kathmandu, Nepal.

The Dietary Approach to the Management of Diabetes (DIAM-D) trial is a hospital-based, open-label, two-armed, randomized control trial. A total of 156 participants with T2DM having HbA1c >6.5% will be enrolled in the study. Participants will be consecutively enrolled and assigned to receive nutrition education and counseling (NEC) and diet plan in the intervention group (n=78) and usual routine care in the control group (n=78) randomly. The NEC will be provided to participants on group session and the diet plan will be face-to-face individual basis at the time of enrollment and follow-ups will be done every month. Baseline data will be collected using a structured questionnaire for an interview and the biochemical tests will be measured. Baseline data will be collected at the time of enrollment, midline in three months and end-line data collection in 6 months. The primary outcome of the study will be a difference in mean change (from baseline, midline to 6 months) in the HbA1c level between the two study arms from baseline to end line. The secondary outcomes measure will be changed in biochemical and clinical parameters between the two arms at baseline midline to six months. Data will be entered using Epidata Software and transferred to the STATA/MP version 14.1 for further analysis. Data will be analyzed using an intention-to-treat basis. Independent sampele t-test will be used to estimates changes between the intervention and usual care arms.

**Key word:** Dietitian, Dietary approach, Management, Diabetes, Nepal

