## **7.2. Types of study**

a. Experimental/Interventional: The proposed study is a randomized, controlled, open-label trial to evaluate the effectiveness of dietitian-led dietary approach to management of diabetes on reduction of HbA1c level and macronutrient intake among T2DM patients in tertiary care hospital in Kathmandu, Nepal (Figure 2). This study utilized two-arm RCT with equal allocation of participants between the intervention and control group/usual care arm. The intervention will include a dietitian-led nutrition education, counseling session and individual basis diet plan emphasis on glycemic control diet targeted to T2DM patients attending during the OPD visits in hospital.

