# **Plan for data management and statistical analysis**

- **Data entry:** A data entry program will be developed using EpiData version 3.0. A number of skips and ranges will be developed to ensure data entry. Trained data entry professionals will enter the data. After the data entry, a thorough check and cleaning of data will be done to maintain consistency.
- **Data analysis:** Data will be analyzed on an intention-to-treat analysis. Data will be analyzed using STATA/MP version 14.1 (StataCorp LP, College Station, Texas). A number of statistical analysis will be done to analyze the data which are listed below:
- **Normality test:**The normality of data will be assessed using the Kolmogorov-Smirnoff test and visual inspection of Q-Q plots. Normally distributed data will be presented as means with standard deviation whereas non-normally distributed data will be expressed as medians with interquartile ranges.
- **Descriptive statistics**: Descriptive statistics will be carried out for socio-demographic information. Frequency, percentage, mean (standard deviation) and median (inter-quartile range) will be calculated under descriptive statistics.
- **Chi-square test**: Chi-square or Fisher exact test will be used to analyze between the intervention and usual care arm for categorical variables.
- **Independent sample t-test:** Difference between intervention and usual arm will be applied using independent sample t-test assuming equal variance if data is normally distributed for continuous variables (two-tailed; parametric).
- **Mann-Whitney U test**: Mann-Whitney U test will be used to compare the medians of continuous variables if in case the assumption for independent sample t-test will be violated (two-tailed; non-parametric).
- **Linear regression**: A linear regression analysis will be used to model the primary and secondary outcome measures.

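### The step from 54 to 78 per arm matches adding the two loss rates and multiplying by 1.45; dividing by the retained fraction gives 72 or 90, depending on what non-response means

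*Protocol*

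**What the plan says.** The sample size section of the protocol sets the target by "taking α level of significance at 5% and power of 90" per cent, with the two-sided normal quantile 1.96. It concludes: "The sample size will be calculated 108 (54 participants in each arm"). The next sentence says that this number is "adjusted with 20% non-response rate and 25% loss through follow-up and drop out the total sample size will be 156", split as 78 and 78. It prints no formula for the adjustment and does not define non-response.

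The project summary fixes what the 156 are: "A total of 156 participants with T2DM having HbA1c >6.5% will be enrolled in the study". Section 7.12 enrols a person once the consent form is signed and then randomises. Section 7.7 lists consent among the inclusion criteria.

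**The concern.** A sample size is inflated so that the required number is still evaluable after the expected losses. The required number must therefore be divided by the fraction retained. Adding the loss percentages and multiplying understates what is needed whenever both losses act on the people counted. Moreover, if one of the losses happens before anyone is counted, it does not belong in the calculation at all.

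The sentence offers 156 as the number that protects 54 evaluable per arm, and with it 90% power, against the stated losses. As written, a reader cannot tell whether it does, because that depends on a term the protocol leaves undefined.

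**Working it through.** **Inputs.** Required evaluable number 54 per arm, losses of 20% and 25%, and enrolled number 78 per arm (protocol, sample size section). Two-sided 5% level and 90% power (same section: 1.96 and 1.282). Equal allocation (section 7.2). Two-tailed equal-variance t-test (statistical analysis section). Difference: the printed d of 0.64 in absolute value, or 0.63 from the quoted source means (10.30 - 9.67).

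**Step 1. Reproduce 78.**
- 54 x (1 + 0.20 + 0.25) = 54 x 1.45 = 78.3, and 108 x 1.45 = 156.6. These match 78 and 156.
- Other routes do not: 54/0.80 = 67.5; 54/0.75 = 72; 54 x 1.20 x 1.25 = 81; 54/0.80 x 1.25 = 84.4; 54 x 1.20/0.75 = 86.4; 54/(0.80 x 0.75) = 90; 54/0.55 = 98.2.

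The multiplier is an inference, but it is the only route tried that gives the stated figure.

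**Step 2. Inflate by the retained fraction.**
- Only the 25% loss falls on enrolled patients: 54/0.75 = 72 per arm, 144 in total.
- Both losses fall on enrolled patients, one after the other: 54/(0.80 x 0.75) = 54/0.60 = 90 per arm, 180 in total.

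Neither is 78.

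**Step 3. What 78 per arm leaves.**
- 25% loss only: 78 x 0.75 = 58.5, about 58 evaluable, above 54.
- Both losses: 78 x 0.60 = 46.8, about 47 evaluable, 7 short of 54.
- Break-even: 1 - 54/78 = 30.8%. The 25% loss is inside this limit. The combined loss of 40% (1 - 0.60) is outside it.

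**Step 4. The SD behind 54.** The normal formula is n per arm = 2 x [SD x (1.96 + 1.282)/d]^2.
- Printed S = 0.1, d = 0.64: n = 0.51, so 1 per arm. This cannot be the input that gave 54.
- SD = 1.0: n = 51.3 at d = 0.64 and 52.9 at d = 0.63. The t-test version needs 53 and 54.
- Solving back from 54 per arm gives an SD of 1.01 (d = 0.63) to 1.03 (d = 0.64).

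The power figures below therefore assume SD = 1.0.

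**Step 5. Power of the two-sided 5% t-test (noncentral t, SD = 1.0).**

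| Evaluable per arm | d = 0.63 | d = 0.64 |
| --- | --- | --- |
| 46 | 84.8% | 85.9% |
| 47 | 85.6% | 86.7% |
| 54 | 90.0% | 90.9% |
| 58 | 92.0% | 92.8% |

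The normal approximation gives 86.2-87.2% at 46.8 per arm and 92.6-93.3% at 58.5 per arm.

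**The case against.** The strongest case for the plan is that enrolment is safe as it stands. The 156 are people who have already consented, so refusal when approached happens before anyone is counted. Only the 25% loss then acts on them, about 58 per arm remain, and 78 is 6 more than the 72 needed. This stands, and it is the more natural reading. It does not rescue the sentence, which lists non-response among the allowances that turn 54 into 78.

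A reader might infer from the faulty multiplier that the trial is underpowered. The documents do not support that as a general statement. The shortfall arises only if both losses apply to enrolled patients, and nothing in the protocol says that they do.

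A second objection is that any power figure here rests on an SD that the protocol does not state. That is also right. With the printed S = 0.1, power would be near 100% at every number in the table.

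Nor is this the largest doubt in the section. The source results, quoted as "was 9.67±0.29 Vs 10.30±0.29 respectively", carry standard errors, and the source's arm sizes are not given. If those arms held 30 to 54 patients (an assumption), 0.29 x sqrt(n) gives an SD of about 1.6 to 2.1. Power at d = 0.63 would then be roughly 33-53% even with 54 evaluable per arm. That is a separate matter. It does not affect how 54 became 78, but it is a reason not to write a new power figure into the protocol before S is settled.

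**Conclusion.** The adjustment is wrong as written on either reading: 78 is neither the 72 needed for the 25% loss alone nor the 90 needed for both losses. This part does not depend on the SD. That the rates were added and multiplied is inferred from the match with 78.3.

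The consequence for power is conditional. If non-response is refusal before consent, the 90% target is met with a small margin (about 92-93%), and the fault is a misplaced allowance. If both losses fall on enrolled patients, the target is missed by about 3 to 5 points (about 85-87%). Both ranges rest on an SD of about 1.0, d of 0.63 to 0.64, and 54 per arm taken as the correct requirement. The point calls for a correction to the text; it does not establish a loss of power.

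**What to change.** Keep 156. In the sample size section:

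1. Define non-response and state which losses occur after randomisation.
2. If non-response is refusal before consent, take the 20% out of the enrolled number and use it to set how many patients must be screened or approached.
3. Divide by the retained fraction for the losses that remain, and show the formula.
4. State the evaluable number per arm that 78 leaves: about 58 under the 25% loss alone, or about 47 if both losses apply.
5. Restate the resulting power with the SD and d used, but only after the printed S has been reconciled with the 54 per arm. Until then, any power figure should carry the condition that it assumes an SD of about 1.0.

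The cost is a rewritten sentence or two. Enrolment, conduct and analysis do not change. If both losses do apply after enrolment, the stated power falls by about 3 to 5 points under the same SD assumption.

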## **7.7. Inclusion and Exclusion criteria**

**Inclusion Criteria:**

- Diagnosis of type 2 diabetes
- HbA1c>48 mmol/mol (6.5%) at time of diagnosis ^21^
- male or female aged ≥24-64 years and visited in OPD of target hospital
- Those who give consent to participate in our intervention study

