## **7.3. Study population/Sampling frame**

The source of the population of the study in both intervention and control group will be known cases of T2DM and newly diagnosed cases of T2DM patients who are within 25-64 years of age group attending the OPD of the hospital.

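### The HbA1c floor is tied to the time of diagnosis although known cases are eligible, so patients now at or below 6.5% can enrol and dilute the difference the trial is sized for

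*Protocol*

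**What the plan says.** Four places in the Protocol bear on who may enter with respect to HbA1c.

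- **Section 7.7, Inclusion Criteria:** "HbA1c>48 mmol/mol (6.5%) at time of diagnosis".
- **Section 7.3, Study population:** the source population is "known cases of T2DM and newly diagnosed cases of T2DM patients who are within 25-64 years of age group".
- **Section 7.7, Exclusion Criteria:** patients at or above 93 mmol/mol, printed as equal to 10.5%, are excluded. No time point is given.
- **Project summary:** "A total of 156 participants with T2DM having HbA1c >6.5% will be enrolled in the study". No time point is given here either.

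The outcome and the sizing also matter. The summary states: "The primary outcome of the study will be a difference in mean change (from baseline, midline to 6 months) in the HbA1c level". The Sample size section takes its planning values from a South African trial in which the "mean+ SE of HbA1c percentage in both intervention and control group was 9.67±0.29 Vs 10.30±0.29 respectively". It uses a difference of 0.64 with 90% power at a two-sided 5% level, and arrives at 54 per arm before allowance for losses.

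**The concern.** For a newly diagnosed patient, HbA1c at diagnosis and HbA1c at enrolment are nearly the same measurement. For a known case they may be years apart, with treatment started in between. Because the only floor is attached to the earlier value, a treated patient now at, say, 6.0% satisfies every listed criterion.

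That matters because the primary outcome is the change in HbA1c. A patient already at or below 6.5% has little room to fall, whichever arm he or she is in. Each such patient pulls the average difference between arms towards zero, while the sample size assumes the full 0.64 points. The trial would then run below its stated 90% power, and the population to which the result applies would not be the one the summary describes.

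**Working it through.** **1. The passages side by side.** Take a known case diagnosed at 8.0% and now at 6.0% on oral treatment.

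| Place | Requirement | Does this patient fit? |
|---|---|---|
| 7.3 | known or newly diagnosed case | yes |
| 7.7 inclusion | above 6.5% at diagnosis | yes |
| 7.7 exclusion | at or above 93 mmol/mol (10.5%), no time point | not excluded if current value is used |
| Project summary | enrolled patients have HbA1c above 6.5% | no, on the plain reading |

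Section 7.10 plans an HbA1c at baseline, but no section uses it as a lower entry limit.

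**2. The plan's own sample size.** Inputs from the Sample size section: Zα/2 = 1.96, Zβ = 1.282, d = 0.64, S printed as 0.1. Formula: n per arm = 2(1.96 + 1.282)² S² / d².

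- With S = 0.1: 2 × 10.511 × 0.01 / 0.4096 = 0.51, so 1 per arm, not 54.
- With S = 1.0: 2 × 10.511 × 1 / 0.4096 = 51.3, so 52 per arm. With the observed difference 10.30 − 9.67 = 0.63 it is 53.0, so 53 per arm. The t-based calculation for 0.63 gives 53.9, so 54.

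The stated 54 is therefore consistent with an SD of 1.0 and not with the printed 0.1. I use SD 1.0 below as an assumption. The misprint or error in S is a separate matter.

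**3. Dilution.** Let f be the share of enrolled patients at or below 6.5%, and r the effect in them relative to the others. The average difference becomes d = 0.64 × [(1 − f) + f × r]. The documents give neither f nor r, so both are assumed over a range. Power is from the two-sided 5% t-test (noncentral t) with 54 per arm and SD 1.0. Undiluted power is 91%.

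| f | d if r = 0 | power | d if r = 0.5 | power |
|---|---|---|---|---|
| 10% | 0.576 | 84% | 0.608 | 88% |
| 20% | 0.512 | 75% | 0.576 | 84% |
| 30% | 0.448 | 64% | 0.544 | 80% |
| 40% | 0.384 | 51% | 0.512 | 75% |

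For r = 0, restoring 90% power would need about 65 evaluable patients per arm at f = 10% and about 82 at f = 20%, against 54 planned.

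**4. Side items in the same eligibility text.** By the standard conversion (assumed; the Protocol does not print it), % = 0.09148 × mmol/mol + 2.152. Then 93 mmol/mol is 10.66% and 10.5% is 91.3 mmol/mol, so a patient at 10.6% is excluded by one unit and not by the other. The lower age limit is 25 in section 7.3 and 24 in section 7.7.

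**The case against.** The strongest reply is that the criterion may be deliberate. A threshold at diagnosis confirms that the patient has diabetes, and an effectiveness trial in outpatients may accept varied control. The specific objectives also include knowledge, macronutrient intake, BMI and waist-hip ratio, for which well-controlled patients are informative. This stands as a reason not to insist on one resolution. It does not remove the need to choose, because the summary and the sizing then have to reflect that choice.

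A reader might infer that the summary and section 7.7 flatly contradict each other. The documents do not go that far. The summary gives no time point, so the conflict rests on reading it in its ordinary present sense. On the kindest reading, the summary merely leaves out the qualifier.

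A reader might also infer that the trial would be biased. It would not. Section 7.12 randomises every eligible patient, so well-controlled patients fall into both arms in expectation and the comparison stays unbiased for the population enrolled. What changes is that population and the power.

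Finally, the power figures depend on assumptions. The zero-effect column is the worst case and should not be quoted alone. The reported SE of 0.29 may point to an SD above 1.0 (at an assumed 20 per arm, 0.29 × √20 = 1.3), which would lower every figure, including the starting 91%. Losses smaller than planned would raise them. None of this alters the direction.

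**Conclusion.** The point holds as a gap in the timing of the HbA1c floor. As written, the Protocol admits known cases now at or below 6.5%. They do not match the summary's description and have little scope to improve on the primary outcome. The direction of the effect on power is clear; its size is not known from the documents. Under SD 1.0, 54 per arm and a 10 to 40% share of such patients, power lies between 88% and 51% instead of 91%, depending on the share and on whether those patients gain half the effect or none. It would go beyond the evidence to say that the trial is underpowered by any particular amount. The unit and age mismatches are real but editorial, and add no weight to this point.

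**What to change.** State in section 7.7 that both HbA1c limits, lower and upper, apply to the baseline sample taken before randomisation, which brings the list into line with the Project summary. If well-controlled patients are meant to be enrolled, keep the diagnosis-based wording, correct the summary, and revise the assumed difference and the sample size for that broader population. As minor corrections, reconcile the two units of the upper limit and make the age limits in sections 7.3 and 7.7 agree.

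The cost is small. Baseline HbA1c is already planned in section 7.10, so no extra test is required. The result must, however, be available before a patient is randomised, and the eligible pool becomes somewhat smaller.
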